### Arms of the Study

#### Treatment as Usual Group

ACL rehabilitation is an exercise group using evidence-based milestones to progress through a mix of strength and neuromuscular control exercises. Stages 1 and 2 are weekly, and stages 3 and 4 are every 2 weeks. Those who consent and are randomized to the usual care group will have a usual induction to the ACL rehab program, including

Recommended amount of exerciseTypes of exercise (personalised, related to goals)Appropriate use of ice, crutches, or bracing as individually indicatedEducation on potential red flags, expected milestones, and challenges of each stage

Patients will progress through the 4 phases of rehabilitation according to their ability. At each face-to-face session they will be assessed by their physiotherapist for quality of movement, strength, and neuromuscular control toward goal achievement.

#### Intervention Group

If randomized to the intervention arm, patients will have initial education on the use of TRAK to support their rehabilitation. They will be offered follow-up teaching sessions if required. Patients will have access to the 5 dimensions of TRAK:

Contact with the physiotherapist via emailExpert knowledge base for each stage of the program detailing milestones, common problems, and a summary of the evidence baseIndividualized exercise program chosen by their physiotherapist, including videos and instructions of each session. There is a technique guide that advises the patient how to do the exercises correctlyExercise log to record exercise participation, progressions, and measures of leg strength and effort levelPrompt system to remind patients to adhere

At each face-to-face session patients will be assessed by their physiotherapist for quality of movement, strength, and neuromuscular control and appropriate progressions toward goal achievement. Their exercises will be modified on their TRAK interface to reflect progress. Use of behavior change tools like logs, goal reviews, and use of prompts are recorded with usage data.

### Outcome Measures

Patients will complete outcomes at 6 weeks, 3 months, 6 months, and final visit. This is in line with previous RCTs in the field [6,31-33].

#### Primary Outcomes

RecruitmentRetentionUsage such as log-ins, number of pages visited, response to prompts, and log use will inform influence of behavior change toolsCost analysisFace to face time with physiotherapistsNumber of appointmentsConsultant visitsGeneral practitioner visitsEmail contactsPhysiotherapist time outside of class

#### Secondary Outcomes

Patient-rated outcome measures (PROMs) are chosen as the most likely outcome measures for use in a full RCT, depending on feasibility results.

Knee Injury and Osteoarthritis Outcome Score [34]Health Resource Use Questionnaire [35]Stanford Self-Efficacy Questionnaire [36]EQ-5D-5L [28]

####  Usage of TRAK Website

Log-insPages visitedLog inputStrength progressions inputStrength gains (Limb Symmetry Index and Return to Sport After Injury Scale)Email contacts to physiotherapists

### Adverse Events

Adverse events such as infection, reinjury, or failure to progress are rare but will be monitored throughout at face-to-face sessions and via patient-clinician email. Patients will be alerted to these possibilities in their inductions, in the class, and on the TRAK website.

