## Introduction

### Background

Anterior cruciate ligament (ACL) rupture is a relatively common injury among those who are physically active [1-3]. Surgery is still the most common way to manage these patients and rehabilitation is essential [1-5] for “maximizing potential for patients to live a full and active life within their family, social networks, education/training and the workplace where appropriate” [5]. The optimal way for delivering rehabilitation is not clear, and current methods vary widely across the world [6-8]. Evidence for treatments is much discussed in the literature. This study addresses how current methods of service delivery in the National Health Service (NHS) struggle to cater to large volumes of patients and the lengthy time span over which rehabilitation is delivered [9-11]. Costing ACL rehabilitation in the NHS is not currently possible given that no standard guideline of care exists.

Some of the challenges of ACL rehabilitation include patient adherence, quality and type of exercises, motivation, and incomplete rehabilitation [3,4,6-8]. eHealth, defined as the use of the Internet in healthcare [12], could improve ACL rehabilitation when used as a tool to support behavior change and greater self-management [13,14]. To date, the use of eHealth has been successful at delivering behavior change to a number of diverse patient groups [12,15-17].

Taxonomy for the Rehabilitation of Knee Conditions (TRAK) is a website that targets behavior change to support self-management. It provides an individualized exercise program, progress log for key exercises, information section for each stage of rehabilitation, prompts, and videos and instructions to support the quality of rehabilitation [18] (see Multimedia Appendix 1). Patients log in to a personal account and have an embedded email link to the physiotherapist who oversees their program.

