### Potential Ethical Considerations

Ethical approval will be sought from the Health Research Authority. There is a risk that using TRAK will not address an individual patient’s needs. The risk of this has been minimized by conducting a series of development research projects leading up to this study.

There is a risk that the participant’s symptoms deteriorate but remote monitoring through email will not identify this quickly. Since face-to-face treatment still applies and the patient can be identified when attending the group, this risk will be minimized. Patients will also be encouraged to air concerns with their therapist via email through the website.

There is a burden of time placed on the patient whereby they have to learn to use the website and take the time to log in daily. However, participants will have access to many aspects of TRAK beyond completion of the study through remote log-in, and using TRAK for some individuals will mean that rehabilitation can fit in better around their lifestyle.

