### Sample Size 

Eligible and consenting patients will be recruited from a North London physiotherapy department. Patient recruitment will begin following completion of preliminary work packages on July 1, 2018. There are on average 2 new patients per week in the ACL group based on local audit data, which equates to 60 patients over 30 weeks who may be eligible for recruitment. There is potential for 15 further patients to be recruited from the first phase of rehabilitation bringing the potential recruits to 75 patients [29,30]. As the inclusion criteria are broad, it is expected that most patients will be eligible, and early patient feedback indicates patients will be keen to partake. Recruitment stops after 30 weeks, which allows the last recruited patient 7 months to participate. This is enough time to deliver on the study objectives of measuring feasibility although not necessarily enough time for patients to complete the program [30].

A sample size of 35 in each arm is recommended in feasibility studies in order to provide sufficient data and precision of means and variances to inform a future randomized controlled trial (RCT) [30]. Once patients have given consent, baseline measures will be collected. Each participant will then be randomized to either treatment or standard care group. This will be done through an online randomizing service. All will be given standard induction and then a TRAK induction for the intervention arm.

Retention will be measured by follow-up outcomes at markers of 6 weeks, 3 months, 6 months, and end of care or the trial. Usage of the website to determine uptake will be measured by the frequency of log-ins, email contacts, and attendance at face-to-face sessions. This will inform the retention rate and the engagement of patients with the intervention.

To assess the acceptability of the website as a self-management support tool, the patients in the TRAK arm of the study will not be obliged to attend weekly face-to-face sessions (although a minimum attendance will be stipulated). Attendance becomes a key measure of self-efficacy, where less face time may indicate greater self-efficacy and therefore informs the possibility of reduced face time for eHealth users in a future RCT. 

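### Adverse events are picked up at sessions and by email, two channels that differ by arm, so event counts by arm would partly reflect how each arm is observed

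*Protocol article*

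**What the plan says.** All references are to the protocol article.

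- **Adverse Events** names two detection channels: events "will be monitored throughout at face-to-face sessions and via patient-clinician email". It names no scheduled adverse-event enquiry. It adds that patients will be warned about these events at induction, in class and on the TRAK website.
- **Sample Size** sets a different attendance rule for the intervention arm: these patients "will not be obliged to attend weekly face-to-face sessions (although a minimum attendance will be stipulated"). It then treats attendance as a measure in itself, because "less face time may indicate greater self-efficacy".
- **Treatment as Usual Group** gives the usual-care schedule, "Stages 1 and 2 are weekly, and stages 3 and 4 are every 2 weeks", with no relaxation of attendance and no email route among its components.
- **Background** places email inside the intervention: "Patients log in to a personal account and have an embedded email link to the physiotherapist who oversees their program". Intervention Group lists email contact among the five TRAK dimensions, and Usage of TRAK Website counts emails to physiotherapists as website usage.
- **Potential Ethical Considerations** acknowledges that a patient may deteriorate and that "remote monitoring through email will not identify this quickly". Its first mitigation is attendance: "Since face-to-face treatment still applies and the patient can be identified when attending the group, this risk will be minimized". Its second is to encourage patients to raise concerns by email through the website.
- **Outcome Measures** schedules collection in both arms at 6 weeks, 3 months, 6 months and the final visit. **Methods for Protecting Against Bias** has a blinded physiotherapist collect the patient-rated measures. Neither section is named as a source of adverse events.

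**The concern.** A count of adverse events by arm can be read as a comparison only if events have a similar chance of being found in each arm. Here that chance depends on allocation. Face-to-face contact may be less frequent under TRAK, while written contact with the physiotherapist is described only for TRAK. Reminders of what to look for also reach TRAK patients through one extra route, the website.

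Fewer events recorded under TRAK could mean fewer opportunities to see them. More could mean an easier way to report them. A reader of the results could not tell either from a real difference.

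There is also a question of internal fit. The ethics section answers the risk of slow detection by pointing to group attendance, and the Sample Size section relaxes attendance in the arm that relies on remote contact. Because low attendance may be read as self-efficacy, a patient who stays away because of a problem could be counted as managing well.

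The study is meant to test data collection for a full trial. An unequal method of finding events could be carried into that trial, and no later analysis can recover events that were never recorded.

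**Working it through.** The article gives no adverse-event rate, detection rate or safety calculation, so there is no stated figure to reproduce. The check is a comparison of the text, followed by two illustrations on stated assumptions.

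**1. Channels by arm**

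| Channel | Usual care | TRAK |
|---|---|---|
| Face-to-face sessions | Weekly, then every 2 weeks; no relaxation stated | Weekly attendance not required; minimum to be set, not quantified |
| Email to physiotherapist | Not listed | Embedded in the TRAK account |
| Alerts to possible events | Induction, class | Induction, class, website |
| Scheduled event questions | None named | None named |

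No channel named for adverse events is described as the same in both arms. The one contact schedule common to both, the outcome time points, is not used for this purpose.

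**2. Face-to-face detection occasions (illustration)**

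The session frequencies are from the article. The stage lengths and attendance shares are assumptions. Over 26 weeks, with the weekly stages lasting w weeks:

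scheduled sessions = w + (26 − w)/2

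- w = 8: 8 + 18/2 = 17
- w = 16: 16 + 10/2 = 21

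If TRAK patients attend 50% of these, they have 8.5 to 10.5 occasions. At 75% they have 12.75 to 15.75, and at 100% there is no gap. The usual-care figure of 17 to 21 assumes full attendance, which the article does not promise: its Background names adherence as a challenge. The unquantified minimum decides how large the gap may become.

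**3. Effect on recorded counts (illustration)**

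Expected recorded events per arm = n × true risk × share detected. The arm size n = 35 is from the Sample Size section. The risk (equal in both arms) and the detection shares are assumptions.

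| True risk | Usual care, 90% detected | TRAK, 70% detected | TRAK, 50% detected |
|---|---|---|---|
| 5% | 35 × 0.05 × 0.9 = 1.57 | 1.22 | 0.88 |
| 10% | 35 × 0.10 × 0.9 = 3.15 | 2.45 | 1.75 |
| 20% | 35 × 0.20 × 0.9 = 6.30 | 4.90 | 3.50 |

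The ratio of recorded events, TRAK to usual care, equals the ratio of the detection shares, whatever the risk: 0.7/0.9 = 0.78 and 0.5/0.9 = 0.56. If email makes detection better under TRAK (70% in usual care, 90% in TRAK), the ratio is 0.9/0.7 = 1.29. The article does not settle which case applies.

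**4. Would the artefact be noticed?**

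Across these scenarios, an approximate two-proportion calculation gives a 4% to 16% chance that the spurious difference reaches two-sided 5% significance. With counts this small the approximation is rough. It shows that the distortion would seldom stand out, and equally that it would seldom produce a false significant result.

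**The case against.** **No safety comparison is planned.** Adverse events are in neither the primary nor the secondary outcome list, and the article speaks only of monitoring. This stands and limits the impact. It does not remove the point, because events from a two-arm study are likely to be described by arm and would inform the next trial.

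**A reader might infer that the attendance rule contradicts the safety mitigation.** The text does not support that. A minimum attendance will be set, so face-to-face treatment does still apply under TRAK, and email is offered as a second safeguard. The mitigation is weakened by an unknown amount. It does not help that the second safeguard is the route the same section has just described as slow.

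**A reader might also infer that usual-care patients have no email access.** The article never says so. The Adverse Events section does not limit email to one arm, and email contacts also appear among the cost items under Primary Outcomes. That email belongs to TRAK alone is a strong inference from how it is described throughout, not a stated fact.

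**Other data could reveal events.** The Health Resource Use Questionnaire, the knee score, and recorded general practitioner and consultant visits could show some problems, and TRAK patients also keep exercise logs. This is fair, and it means TRAK cannot be called the less closely observed arm overall. But none of these is named as a source of adverse events, and the logs are again in one arm only.

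**A condensed article may leave adverse-event forms and the attendance minimum to the full protocol.** This is true of the forms and the figure, and their absence is not the criticism. The criticism is of the two channels that the article does name.

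**Conclusion.** The concern holds in a limited form. Followed as written, the plan detects adverse events through two channels that are both described differently by arm, so counts by arm would partly reflect observation. The direction cannot be predicted: fewer sessions would lower the TRAK count and email would raise it.

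Under the assumed detection shares, the ratio of recorded events with no true difference runs from 0.56 to 1.29. At 10% risk and 35 per arm, the gap is about one event. Those shares, the risks, the stage lengths and the attendance levels are assumptions. Only the arm size and the session frequencies come from the article.

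The impact is moderate, because this is a feasibility study with no planned safety test. It is still worth correcting before recruitment, because unequal collection cannot be repaired at analysis and the method may carry into the full trial.

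**What to change.** 1. Add one short, identical set of adverse-event questions (infection, reinjury, failure to progress) to the outcome collection already scheduled at 6 weeks, 3 months, 6 months and the final visit. Use it in both arms, whether or not the patient attends sessions.
2. Use these answers as the primary basis for any description of events by arm.
3. Do not discard other reports. List all events found at sessions or by email, by source and arm, with the number of sessions and emails per arm so that readers can judge the opportunity for detection. Appointments and email contacts are already to be counted.
4. Reconcile Potential Ethical Considerations, Sample Size and Adverse Events on how deterioration is identified in patients who attend less often, and state whether usual-care patients have an email route. The attendance level itself is a clinical matter for the investigators.

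The cost is a few extra questionnaire items at existing time points, a small added burden for patients, and some clarifying text.

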### Methods for Protecting Against Bias

With the help of the clinical trial unit, an online randomizing process will be used for this trial to help control against bias. A physiotherapist who is blinded to treatment allocation will collect PROMs from patients. PROMs by their nature are bias-limiting because they are filled in by patients and not clinicians.

### Data Analysis and Frequency of Analysis

Standard procedures of data collection will be adhered to and guided by practices of the clinical trials unit. The qualitative and quantitative data strands are to be collected and analyzed simultaneously and with equal priority [23].

Quantitative data will be analyzed as follows: binary and other categorical measures will be summarized using frequencies and percentages and continuous measures using means and standard deviations (or medians and interquartile ranges for very skewed distributions). All outcome measures will be summarized separately by study arm. Differences in outcomes between arms will be estimated using multilevel linear or logistic regression models with a random effect of person to account for the repeated measures on individuals over time. Potential therapist effects will be appropriately modelled. The precision of estimates will be assessed using 95% confidence intervals. Power analyses will be conducted to calculate the sample size necessary to detect an effect of the intervention in a future RCT. 

The qualitative analysis will be done using a thematic analysis approach. This sees the data itself, rather than the theory, driving the process. The themes emerging from the interviews are grouped stringently so all the interview data relating to a particular theme are recorded. An explicit process of analysis will be outlined and reported, especially with regard to how data are weighted and reported secondary to frequency of occurrence or explanatory value [37]. The process will be largely inductive and will develop an epistemology of the ACL patient experience where preconceived ideas are suspended in favor of the unique perspectives of the participants. The patient’s “perception, thought, memory, imagination, and emotional experience of an event” is liberated and fully informs our understanding [38]. Interview data will be analyzed by the chief investigator and cross-checked by another supervisor.

Expected outputs:

Determining the feasibility of an RCT by gathering sufficient data to power a trial as outlinedDetermining the acceptability of TRAK as a tool of behavior change to physiotherapists and patients and illuminating the mechanisms that influence feasibility measuresDetermining the feasibility of gathering costing data to inform an economic analysis alongside a potential RCT

### Patient and Public Involvement

Participant feedback will be sought from the patient steering group at quarterly meetings throughout the trial or by request. Patients were part of the design of TRAK, and they informed the content and filmed the exercise videos. They checked all lay project documents for the ethics process. A National Institute for Health Research PPI panel reviewed the study favorably, and changes were made based on feedback.

## Results

Recruitment to this study will be pending successful funding of the study. Recruitment will aim to begin in July 2018 following completion of preliminary work packages. Ethical approval will be sought through the Health Research Authority in January 2017 pending successful funding of the study. The study will be overseen by a trial steering committee.

## Discussion

Impact of the study will be the delivery of TRAK ready to test in an RCT at the end of the feasibility study. The feasibility of collecting data toward a phase 3 effectiveness and cost-effectiveness study and the future direction of eHealth interventions in the management of ACL patients in the NHS will be established.

## Appendix

Multimedia Appendix 1 Images from the Taxonomy for the Rehabilitation of Knee Conditions website.

## Abbreviations

ACL: anterior cruciate ligament
NHS: National Health Service
NICE: National Institute for Health and Care Excellence
PPI: patient and public involvement
PROM: patient-rated outcome measure
QALY: quality-adjusted life-year
RCT: randomized controlled trial
TRAK: Taxonomy for the Rehabilitation of Knee Conditions
